## Study aims and hypotheses

Because of the promising characteristics of JITAIs for behavioral activation in depression, our goal is to develop and evaluate JITAIs that target behavioral activation for depression. This will involve a design phase, in close collaboration with individuals with depression and therapists, and an evaluation phase to assess feasibility, acceptance, and preliminary effectiveness. We hypothesize that (1) it will be feasible and acceptable to deliver JITAIs to patients receiving treatment for depression, (2) JITAIs will result in improved proximal outcomes in terms of depression and well-being compared with not receiving JITAIs, and (3) behavioral activation with JITAIs will result in improved distal outcomes from baseline to post-treatment compared with TAU in terms of depression, well-being, personal recovery, and quality of life.

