They will complete baseline questionnaires (PHQ-9, MHC-SF, QPR, and EQ-5D) and undergo a 1-week baseline period with two EMA surveys per day following a semi-random sampling in time blocks of 1 h (e.g., 09:00–10:00; 12:00–13:00; 15:00–16:00, and 18:00–19:00). Each assessment takes place at random moments in one of the time blocks, and scheduling of the time blocks is decided by the participants at the start of the baseline. After the baseline period, the intervention phase (MRT) will start and last 6 weeks. During the MRT, participants receive four EMA surveys per day—following semi-random sampling in time blocks of 1 h—which serve as a decision point. At each decision point, the participant is eligible for randomization if they (1) completed the EMA and (2) met a prespecified tailoring-variable threshold indicating that they are in the symptomatic half of the item scale (i.e., a vulnerability state for withdrawal/avoidance). Because the EMA includes both negatively and positively valenced items, thresholds are operationalized in a directionally consistent way: for negatively valenced symptom items (e.g., “I feel down,” “I feel tired,” “I feel listless”), eligibility is defined as a score ≥ 4; for positively valenced functioning items (e.g., “I feel energetic”), eligibility is defined as a score ≤ 4. This threshold was selected to identify "moderate-or-worse" vulnerability states where the risk of avoidance is elevated [35] while managing participant burden by preventing prompting during mild or asymptomatic states. If the decision point is eligible for randomization, there is a 50% probability of receiving a JITAI and a 50% probability of receiving no JITAI. Thus, randomization occurs repeatedly within participants across eligible decision points. Allocation to the TAU + JITAI and TAU groups is not randomized. Within the TAU + JITAI condition, randomization at eligible decision points is generated automatically by m-path (simple randomization), and recruiters do not have access to future assignments. Because of the nature of the intervention, participants, therapists, and researchers are not blinded to study condition; therefore, no formal blinding or unblinding procedures apply.

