For each participant, the tailoring variables will represent (1) one of the EMA items assessing depressive symptoms that exhibited the highest average score during their baseline period, and (2) one of the EMA items assessing depressive symptoms that the participant rated as “most impactful” on their daily functioning identified via a shared decision-making procedure following the baseline week. Specifically, a researcher and the participant jointly review visualized baseline EMA data (e.g., timeline plots of the symptom items), and the participant identifies which symptom most hindered their daily functioning and/or engagement in planned activities. This self-identified symptom is operationalized as the “impactful” tailoring variable. At the end of each study day, participants will receive an EMA survey that does not serve as a decision point. Two questions are added to the evening survey (activity level and best moment of the day). Importantly, the JITAIs are embedded in a therapist-supported treatment. During weekly therapy sessions, the EMA data collected during the week are visualized (e.g., timeline plots of mood and activities) and reviewed collaboratively by the therapist and participant. This integration aims to support engagement. The questionnaires completed at baseline (PHQ-9, MHC-SF, QPR, and EQ-5D) will be administered again at the start of the JITAI phase and at the end of treatment. In addition, at the end of treatment, participants will complete questionnaires regarding the acceptance of the JITAIs (CSQ-8, SUS, TWEETS). Participants in the TAU group will complete these questionnaires (PHQ-9, MHC-SF, QPR, EQ-5D) at the same time points. Participating patients in the TAU + JITAI group will receive a remuneration of 25 euros when they have completed the questionnaires at the last time point. Therapists will be interviewed at the end of treatment to share their experiences with patients using JITAIs.

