#### Distal outcomes

For the distal outcomes (PHQ-9, MHC-SF, QPR, and EQ-5D), propensity score matching will be used to match participants in the TAU group with those in the TAU + JITAI group. Propensity scores are calculated via logistic regression analysis [38], which models the probability of receiving treatment (TAU + JITAIs versus TAU) as a function of baseline covariates, including sex, age, and severity of depressive symptoms at the start of treatment. After the propensity scores are calculated, participants from the TAU group are matched with participants from the TAU + JITAIs group via a matching method (nearest neighbor matching with a caliper). This method ensures that each participant in the TAU + JITAIs group has a corresponding participant in the TAU group with a similar propensity score, making the groups similar in terms of the matched covariates. The matched sample is then used in a mixed-effects model that considers the paired nature of the matched sample by including the matched pairs as random effects. This ensures the correct estimation of standard errors and appropriate interpretation of the results. The fixed effects in the model include time (baseline, 1-week and 6-week assessment), group status (TAU + JITAIs versus TAU), and their interaction, whereas the random effects model includes variability between matched pairs and within individual participants over time. A significant interaction suggests that changes in the outcomes (PHQ-9, MHC-SF, QPR, and EQ-5D) differ between groups.

Participants may pause or discontinue the JITAI component at their own request, at the advice of the treating clinician. Data collected until then will be used for analyses, and participants will be asked to complete the outcome questionnaires. This will not affect access to TAU, and no protocol-driven modification of TAU is planned. Possible harms are expected to be limited and may include burden, annoyance, or temporary distress related to EMA or prompts. Any adverse events will be documented and discussed with the treating clinician.

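### The distal analysis rests on one group-by-time interaction over three waves, although the middle wave precedes any JITAI, so a significant result need not reflect the JITAI period

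*Protocol article*

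**What the plan says.** **Timing.** Under Evaluation phase, the TAU + JITAI group will "undergo a 1-week baseline period with two EMA surveys per day". Then: "After the baseline period, the intervention phase (MRT) will start and last 6 weeks". The baseline questionnaires "will be administered again at the start of the JITAI phase and at the end of treatment". For the comparator: "Participants in the TAU group will complete these questionnaires (PHQ-9, MHC-SF, QPR, EQ-5D) at the same time points". Table 2 puts the questionnaires in the baseline week, evaluation week 1 and evaluation week 6. It shows no EMA for the TAU group.

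**Model.** Under Distal outcomes (Data analyses), after propensity score matching: "The fixed effects in the model include time (baseline, 1-week and 6-week assessment), group status (TAU + JITAIs versus TAU), and their interaction". On the random part: "the random effects model includes variability between matched pairs and within individual participants over time". The only reading offered is: "A significant interaction suggests that changes in the outcomes (PHQ-9, MHC-SF, QPR, and EQ-5D) differ between groups".

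**Hypothesis.** Study aims and hypotheses states that "behavioral activation with JITAIs will result in improved distal outcomes from baseline to post-treatment compared with TAU".

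**The concern.** The wave labelled 1-week falls before the first JITAI. An interaction across all three waves therefore combines two periods. In the first, no JITAI is delivered but one group self-monitors by EMA. In the second, JITAIs are delivered. Hypothesis 3 asks for one comparison, baseline to post-treatment, and the stated rule does not isolate it.

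This matters more than it would in a randomized trial, because the groups are not randomized. The named matching covariates (sex, age, depressive severity) do not include baseline well-being, recovery or quality of life. Divergence in the first week, from EMA self-monitoring or residual selection, could produce a significant interaction that a reader credits to JITAIs. The distal estimates are meant to inform a future trial, so a misattributed signal would carry forward.

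**Working it through.** **The plan's own figures.** There is no power or precision statement for the distal comparison. The one sample-size figure, for adherence, reproduces:
- JITAIs per participant: 168 × 0.66 × 0.25 = 27.7, about 28.
- Design effect: 1 + 27 × 0.05 = 2.35.
- Half-width: 1.96 × √(0.60 × 0.40 × 2.35 / (46 × 28)) = 0.041.

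The plan thus expects to retain about 46 per group.

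**Assumptions that are not in the documents.** Categorical time, two-sided 5% level, 45 per group, unit SD at each wave, and correlation within matched pairs ignored. Two correlation patterns for (baseline, middle), (baseline, end), (middle, end) are used:
- E: 0.5, 0.5, 0.5, the exchangeable pattern that random intercepts imply.
- U: 0.7, 0.5, 0.6.

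**Method.** Let d be the group difference in change from baseline at the middle and last waves. Its covariance is (2/n)·M, where M is [[1, 0.5], [0.5, 1]] for E and [[0.6, 0.4], [0.4, 1]] for U. The 2-df noncentrality is (n/2)·d′M⁻¹d, referred to the 5% chi-square critical value of 5.99. A 1-df contrast with variance factor v has noncentrality (n/2)·δ²/v.

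**False signal with no JITAI effect**

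| Divergence in the pre-JITAI week | 2-df, E | 2-df, U | Baseline-to-post |
|---|---|---|---|
| None | 5% | 5% | 5% |
| 0.1 SD, gone by end | 7% | 9% | 5% |
| 0.2 SD, gone by end | 15% | 23% | 5% |
| 0.3 SD, gone by end | 29% | 47% | 5% |
| 0.3 SD, persisting | 29% | 39% | 30% |

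For the fourth row:
- E: 22.5 × 1.333 × 0.09 = 2.70, giving 29%.
- U: 22.5 × (1/0.44) × 0.09 = 4.60, giving 47%.

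For the last row, the baseline-to-post noncentrality is 22.5 × 0.09 / 1.0 = 2.03, giving 30%.

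If time is instead linear in weeks 0, 1 and 7 (46 per group, pattern E), the rate for 0.3 SD is about 10% when the divergence is gone by the end and 17% when it persists.

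**Power for a 0.5 SD effect at the last wave only**
- 2-df, E: 22.5 × 1.333 × 0.25 = 7.50, giving 69%.
- 2-df, U: 22.5 × (0.6/0.44) × 0.25 = 7.67, giving 70%.
- Baseline-to-post, 1 df, v = 2(1 − 0.5) = 1: 22.5 × 0.25 = 5.63, giving 66%.
- End of treatment against the mean of both pre-JITAI waves, 1 df, v = 0.75 in both patterns: 22.5 × 0.25 / 0.75 = 7.50, giving 78%.

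The 2-df test is therefore 3–4 points above baseline-to-post and 8–9 points below the contrast that uses both pre-JITAI waves. With correlation decaying over weeks 0, 1 and 7 (0.5 between baseline and end, 46 per group), the three figures are 62%, 67% and 71%.

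**The case against.** **The quoted rule is literally true.** It says that changes differ between groups, not that JITAIs caused the difference. It also leaves open the time coding and the coefficient that carries the conclusion, and such detail may sit in a fuller document. This stands in part: the 2-df test is a reading of the text. But the article does fix the three waves, the interaction and its interpretation, and that stated rule does not match hypothesis 3.

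**The divergence is assumed.** No figure in the protocol supports 0.3 SD in one week, and matching addresses some selection. This stands. The wave alone does not inflate the error rate.

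**Some of the problem is not due to the middle wave.** A persisting divergence also makes the baseline-to-post contrast significant in about 30% of trials. This stands, and is a reason to report the pre-JITAI week separately.

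**A reader might infer that including the wave loses power**, for example 71% on 2 df against 80% on 1 df. That comparison gives both tests the same noncentrality, (1.96 + 0.842)² = 7.85. Here the 2-df noncentrality is 1.33 (E) to 1.36 (U) times that of baseline-to-post, so 80% becomes about 83–84%. A loss against baseline-to-post appears only under other structures, such as the decaying one above.

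**A reader might also infer that the wave labels use two time origins**, one week from baseline and six weeks from the JITAI start. The labels match Table 2's headings equally well (baseline, evaluation week 1, evaluation week 6), so this is at most an ambiguity.

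**Conclusion.** The concern holds in a limited form. The middle wave is a pre-JITAI measurement, and an undifferentiated interaction over three waves does not answer the baseline-to-post question. With categorical time and a 0.3 SD divergence gone by end of treatment, the test is significant in about 29–47% of trials with no JITAI effect, against 5% for the contrast in hypothesis 3. At 0.1 SD the excess is small, and with no divergence there is none. The size and persistence of any divergence, the wave correlations and the time coding are all assumptions.

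The severity is moderate to minor. A reader might take this as a flaw that must be fixed before the trial can be interpreted, but the documents do not support that. The primary outcome is adherence, the Sample size section calls the distal results preliminary, and the Discussion bases progression on adherence and acceptability. The Discussion's caution about the between-group comparison concerns Type II error only, so this false-positive route is not covered by it.

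**What to change.** 1. Keep all three waves and state whether time is categorical or linear.
2. Prespecify one 1-df group contrast at end of treatment per outcome as the basis for the conclusion, preferably with both pre-JITAI scores as the reference. Also report the baseline-to-post contrast of hypothesis 3.
3. Report the group difference in change over the pre-JITAI week separately, as a negative-control check. This is still needed after step 2: with a 0.3 SD divergence, transient or persisting, the contrast against the mean of both pre-JITAI waves is still significant in about 13% of trials (noncentrality 22.5 × 0.15² / 0.75 = 0.675).
4. State the estimand. If EMA self-monitoring counts as part of the package, adjusting for the start-of-JITAI score removes its first-week effect.
5. Clarify whether the 6-week label counts from the start of the JITAI phase.

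The cost is analysis wording only. All the questionnaires are already scheduled in both groups. The one downside is the narrower question in step 4, which reporting both contrasts makes visible.

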#### EuroQol-5 Dimension (EQ-5D)

The EQ-5D [33] is a self-report questionnaire designed to measure health-related quality of life across five key dimensions: mobility, self-care, usual activities, pain/discomfort, and anxiety/depression. Each of the five dimensions is rated on 5 levels of severity, with responses ranging from “no problems” to “severe problems.” The EQ-5D also includes a visual analog scale (VAS), where individuals rate their overall health on a scale from 0 (worst imaginable health) to 100 (best imaginable health).

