#### Sample size

The primary feasibility outcome is dose-received adherence, defined as the proportion of completed JITAIs among all received JITAIs during the MRT phase. A sample size calculation for this outcome was based on the precision of the estimated proportion of completed JITAIs among received JITAIs [39]. Because adherence was defined at the JITAI level, with repeated observations nested within participants, the calculation was adjusted for within-participant correlation using a design effect [40]. During the 6-week MRT phase, participants can have up to 168 decision points (42 days × 4 per day). Assuming participants are available at 66% of these moments and a probability of 25% of receiving a JITAI at a given decision point, participants are expected to receive approximately 28 JITAIs on average. Assuming an adherence proportion of 0.60, a two-sided 95% confidence interval, an average of 28 received JITAIs per participant, and a within-participant intraclass correlation of 0.05, 46 participants would yield an approximate confidence interval half-width of 0.041.

We set the recruitment target for the TAU + JITAI group at 52 participants, comprising the 46 participants indicated by the feasibility-based precision estimate plus 6 additional participants to allow for 13% dropout observed in samples with depression [41]. For consistency in the nonrandomized comparison, we will recruit an equal number of participants in the TAU group. The proximal and distal outcome analyses are intended to provide preliminary estimates to inform a future trial.

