## Discussion

The current study will design JITAIs for behavioral activation in patients with depression and assess their feasibility, acceptability, and preliminary effectiveness. This study aims to develop and examine an innovative approach that may improve adherence to activities related to behavioral activation. If the results of the study suggest that JITAIs are regarded as feasible with > 60% dose-received adherence and acceptable, the intention is to examine JITAIs in a larger trial in the future.

Although it is not recommended to examine effectiveness in feasibility studies [42], we also aim to examine the preliminary effectiveness of JITAIs on proximal outcomes in the current study. For innovative approaches, such as JITAIs, any preliminary estimates of proximal effectiveness are informative for larger trials with more rigorous designs. However, the sample size may not be sufficient for the nonrandomized quasi-experimental design to evaluate changes between groups and increases the likelihood of Type II errors in the between-group comparisons.

In conclusion, there is a need to improve adherence to activities related to behavioral activation in individuals with depression, which may increase its effectiveness. JITAIs offer the potential to improve adherence to activities and have not yet been examined. This study is the first to develop and assess JITAIs for behavioral activation, and will provide data for further research with more rigorous research designs.

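### The distal outcomes are read by significance of the group-by-time interaction, although the plan intends them as preliminary estimates and doubts that the sample is large enough

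*Protocol article*

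**What the plan says.** All references are to the protocol article.

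- **Reading rule (Data analyses, Distal outcomes).** After matching, a mixed model is fitted to each instrument: "The fixed effects in the model include time (baseline, 1-week and 6-week assessment), group status (TAU + JITAIs versus TAU), and their interaction". The only guidance on interpretation is "A significant interaction suggests that changes in the outcomes (PHQ-9, MHC-SF, QPR, and EQ-5D) differ between groups". The section does not mention an effect estimate or an interval.
- **Hypothesis 3 (Study aims and hypotheses).** "behavioral activation with JITAIs will result in improved distal outcomes from baseline to post-treatment compared with TAU", for depression, well-being, personal recovery and quality of life.
- **Purpose (Sample size).** "The proximal and distal outcome analyses are intended to provide preliminary estimates to inform a future trial". The one calculation given concerns the precision of dose-received adherence. The TAU group is made the same size for consistency.
- **Caveat (Discussion).** The sample may not suffice for the nonrandomized comparison, which "increases the likelihood of Type II errors in the between-group comparisons". Type I error is not mentioned.
- **Timing (Procedure, Evaluation phase).** The four questionnaires "will be administered again at the start of the JITAI phase and at the end of treatment". The middle of the three assessments therefore falls before any JITAI can have acted.

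**The concern.** The stated purpose is estimation, while the stated way of reading the results is a test on each of four instruments. A significance reading fits badly here for three reasons.

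1. With four tests and no effect, a stray positive is more likely than 5%. The Discussion does not prepare the reader for it.
2. With about 50 patients per group at most, and fewer after caliper matching, a real but modest effect will usually miss significance. The width of the interval is then the useful information, and it is what the reading rule leaves out.
3. The interaction runs over three time levels. If time is categorical it has two degrees of freedom, and one of its two contrasts lies wholly before the intervention. In nonrandomized groups, early divergence is plausible. It would then count as a difference between groups with no JITAI effect behind it.

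At stake is how a nonrandomized feasibility sample will be reported, and what a later trial team takes from it.

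**Working it through.** **1. The plan's own figure.** The Sample size section gives 168 decision points, 66% availability, 25% probability of a JITAI, adherence 0.60, ICC 0.05 and 46 participants.
- Received JITAIs: 168 × 0.66 × 0.25 = 27.7, about 28.
- Design effect: 1 + (28 − 1) × 0.05 = 2.35.
- Half-width: 1.96 × √(0.60 × 0.40 × 2.35 / (46 × 28)) = 0.041. This reproduces.

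It concerns adherence only. No power or precision is given for the distal comparison, so the figures below rest on assumptions.

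**2. False positives over four outcomes.** Assumed: two-sided 0.05 per outcome and no effect on any. If independent, 1 − 0.95⁴ = 0.185. Simulation of four equally correlated test statistics (1,000,000 draws) gives:

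| Correlation between outcomes | P(at least one significant) | P(at least one significant in favor of JITAIs) |
|---|---|---|
| 0 | 0.186 | 0.096 |
| 0.3 | 0.174 | 0.087 |
| 0.5 | 0.156 | 0.078 |
| 0.7 | 0.130 | 0.065 |
| 0.9 | 0.093 | 0.047 |

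**3. Power and interval width.** Assumed: change from baseline to the final assessment, in units of the outcome SD; within-person correlation r; n analysed pairs; no gain from pairing. The standard error of the group difference in change is √(2 × 2 × (1 − r) / n). For n = 35 and r = 0.6 it is √(1.6 / 35) = 0.214, so the 95% half-width is 1.96 × 0.214 = 0.42 SD. For a true difference of 0.3 SD:

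| Pairs | r | SE | 95% half-width | Power | Mean significant estimate ÷ truth |
|---|---|---|---|---|---|
| 35 | 0.3 | 0.283 | 0.55 | 19% | 2.4 |
| 35 | 0.6 | 0.214 | 0.42 | 29% | 1.8 |
| 35 | 0.7 | 0.185 | 0.36 | 37% | 1.6 |
| 45 | 0.3 | 0.249 | 0.49 | 23% | 2.1 |
| 45 | 0.6 | 0.189 | 0.37 | 36% | 1.7 |
| 45 | 0.7 | 0.163 | 0.32 | 45% | 1.5 |

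At a true 0.5 SD over the same grid, the ratio in the last column is about 1.1 to 1.5. That column applies only to an estimate picked because it was significant. An unselected estimate does not carry this inflation.

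These figures are for a one-degree-of-freedom contrast to the final assessment. They do not describe the three-level interaction.

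**4. What the interaction tests.** With categorical time, the group-by-time term has (2 − 1) × (3 − 1) = 2 degrees of freedom: group difference in change from baseline to 1 week, and from baseline to 6 weeks. The 1-week assessment marks the start of the JITAI phase. Suppose the groups diverge by δ in that first week and then run parallel. Both contrasts equal δ and the interaction is non-null, with no JITAI effect. The contrast to the final assessment equals δ as well. Reporting that contrast therefore does not remove early divergence. It does stop a divergence that has closed by 6 weeks from giving a positive result, and it matches the baseline to post-treatment comparison in hypothesis 3.

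**The case against.** The case on the other side is substantial.

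- The sentence is hedged and explains what an interaction term means, outcome by outcome. A reader might infer that significance on any one of the four instruments would support a claim that JITAIs work. The article does not say so, and the 9% to 19% describes the chance of a stray positive, not the error rate of a stated decision rule.
- A reader might infer that the plan calls the comparison too small, or the analyses solely preliminary. The wording is softer on both counts.
- A reader might infer that an inflated effect will size the next trial. Nothing in the article selects estimates by significance. Progression rests on adherence above 60% and on acceptability, and where the Discussion names estimates that are informative for larger trials, it names proximal ones.
- A leading outcome and a multiplicity rule are optional for exploratory outcomes and may stand in an analysis plan that is not shown. Their absence is no defect here.
- The low power is largely disclosed by the authors themselves.
- The pair numbers, correlations and effect sizes above are assumed.

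All of this stands, and it limits the point. It does not remove the mismatch: the one interpretation rule that is written down is a significance rule, it differs from the purpose written in the Sample size section, and the Discussion warns of only one of the two errors.

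**Conclusion.** The point holds as a mismatch between the stated purpose of the distal analyses and the stated way of reading them. It does not hold as a claim that the plan will declare effectiveness from any single significant outcome, or will pass a selected effect to the next trial.

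If the reading rule is followed, the chance of a stray positive is about two to four times the nominal 5%, a true 0.3 SD difference is missed more often than found throughout the assumed range, and the 95% half-width of about 0.3 to 0.55 SD carries most of the usable information. These sizes rest on two-sided tests at 0.05, 35 to 45 analysed pairs and within-person correlation 0.3 to 0.7, none of which the article gives. The point on the three-level interaction rests on time being treated as categorical, which the article does not state.

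A wording change is worthwhile. The design and the primary outcome are not affected.

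**What to change.** In Data analyses, Distal outcomes, replace the last sentence of the first paragraph with:

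> For each distal outcome, the group difference in change from baseline to the final assessment is reported with its 95% confidence interval. These analyses are exploratory, and no conclusion on effectiveness is drawn from significance.

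In the Discussion, next to the remark on Type II error, add that a significant distal result may be a chance finding, given four outcomes and nonrandomized groups.

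Optional: name PHQ-9 as the leading distal outcome, and state that a distal estimate will not be used alone to size a later trial.

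The cost is wording only; no patients, visits or data change. The sponsor gives up announcing a significant distal result from this sample.
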